### Participant Enrollment

Upon receiving formal authorization from the management of the older adult centers, the nursing director acts as the principal gatekeeper, enabling researcher access to the facility and aiding in the recruitment of prospective participants. Eligible participants are determined by examining health records and MMSE scores in accordance with the inclusion criteria. Individuals who satisfy the requirements are invited to participate and provided with a written information sheet detailing the study’s aim, procedures, and advantages and their right to leave without repercussions. Written informed consent is requested prior to enrollment. For group allocation, participants obtain a group-specific information sheet and sign a corresponding consent form.

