### Trial Design

This multicenter randomized, assessor-blinded trial is structured according to the “max-min-con” principle [45,46]: maximizing experimental variance by ensuring that art activities and art activities with peer group participation are delivered consistently and distinctly from the control condition; minimizing error variance by using standardized protocols for art activities and art activities with peer group participation, trained research assistants (RAs), and reliable measurement instruments; and controlling extraneous variance through minimized randomization and blinding of outcome assessors.

This study has 3 intervention groups: group A (Chinese art activities), group B (Chinese art activities+peer group participation), and group C (regular care), with participants randomized at a 1:1:1 allocation ratio. The study will be conducted consecutively at 3 older adult centers. These 3 centers all belong to Suzhou Health and Elderly Care Industry Development Group Co, Ltd. After on-site inspection, it was determined that the inclusion criteria (affiliation, bed capacity, facilities, management support, and accessibility) were met to ensure feasibility and reasonable representativeness. Each center is treated as a randomization unit. Figure 2 delineates the implementation phase and the data collection procedures in the study. The intervention takes place over 3 sessions in a single week (Monday, Wednesday, and Friday). Baseline evaluations of PWB, loneliness, happiness, relaxation, and salivary cortisol levels are conducted before randomization.

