**Figure 3. F3:**
[figure not shown]
CONSORT (Consolidated Standards of Reporting Trials) flow diagram. CAA: Chinese art activities; DV: dependent variable; PGP: peer group participation; RC: routine care; VAS: visual analog scale.

**Table 1. T1:** SPIRIT (Standard Protocol Items: Recommendations for Interventional Trials) table with the schedule of enrollment, interventions, and assessments.

	Study period					
	Enrollment (T–1)	Allocation (T0)	Intervention session—Monday (T1)	Intervention session—Wednesday (T2)	Intervention session—Friday (T3)	Intervention session—following Monday (T4)
Enrollment						
Eligibility screening	✓					
Information sheet	✓					
General informed consent	✓					
Group-specific informed consent		✓				
Allocation		✓				
Interventions						
Usual care			✓	✓	✓	
Usual care+CAA^a^			✓	✓	✓	
Usual care+CAA+PGP^b^			✓	✓	✓	
Assessments						
PWB^c^ score	✓					✓
Loneliness score—VAS^d^	✓		✓^e^	✓^e^	✓^e^	✓
Happiness score—VAS			✓^e^	✓^e^	✓^e^	✓
Relaxation score—VAS			✓^e^	✓^e^	✓^e^	✓
Salivary cortisol level			✓^e^	✓^e^	✓^e^	✓

a CAA: Chinese art activities.

b PGP: peer group participation.

c PWB: psychological well-being.

d VAS: visual analog scale.

e This includes pretest and posttest assessment.

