### Participant Allocation

The allocation sequence is produced dynamically by an independent statistician throughout the recruiting phase. Each research site serves as a randomization unit. Using the Minimization Random Program software (version 2.01) [54,55], 30 eligible participants are randomly divided into 2 experimental groups and 1 control group in a 1:1:1 ratio, with 10 participants in each group. The confounding variables are age and number of visits per month. A study found that happiness increases with age before the age of 75 years, but for those over 75 years, the probability of happiness begins to decrease. Therefore, participants will be categorized into age groups of 60 to 75 years and over 75 years [56]. The other confounding variable is the number of visits per month. Older people living in institutions tend to meet with family and friends more frequently, often having more positive and less negative feelings [57]. Hence, participants were classified as having visits 1 to 2 times per month or 3 or more times per month. The categories of confounding variables are shown in Table 2.

The researchers will recruit 30 participants from each institution, resulting in a total of 90 older adults (aged 60‐85 years; individuals with ≤1 year of residence) referred by health care providers. In each institution, the 30 participants are allocated into 3 groups—A, B, and C—comprising 10 participants each. Group A is administered Chinese art activities, group B is administered Chinese art activities and peer group participation, and group C receives routine care.

**Table 2. T2:** Categories of confounding variables in the minimized randomization program.

Confounding variable	Category 1	Category 2
Age (y)	60-75	>75
Monthly visit frequency	1-2 times	≥3 times

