For the testing of objectives 1 and 2, a dual test of intra- and intergroup comparisons will be used. If the data are normally distributed, 2-tailed paired-sample *t* tests will be used for intragroup comparison of the Chinese art activities group or the Chinese art activities and peer group participation group. This will test the intervention effects of the Chinese art activities or Chinese art activities with peer group participation interventions on happiness, relaxation, loneliness, and salivary cortisol levels before and after the intervention (3 times). We will use independent-sample *t* tests to compare the effects of the Chinese art activities or Chinese art activities with peer group participation interventions on happiness, relaxation, loneliness, and salivary cortisol levels with the control group. For the testing of objective 3, an independent-sample *t* test will be used to compare the effects of the Chinese art activities with peer group participation and the Chinese art activities interventions on happiness, relaxation, loneliness, and salivary cortisol levels. For the testing of objective 4, salivary cortisol levels will be the main independent variable, and changes in PWB or relaxation will be divided into 3 quartiles as dependent variables. Ordered logistic regression analysis will be used to explore the association between salivary cortisol and these 2 variables. There will be no additional analyses.

Due to the harmless and short-term nature of this study, there will be very little missing data. Preliminary analysis will be conducted based on the complete case. We will use mean imputation for any missing data within a scale. Following the intention-to-treat principle, participants with intervention data will be included in the analysis.

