### Ethical Considerations

This study protocol has been reviewed and approved by the institutional review board of Prince of Songkla University (approval 2024-St-Nur 048). The trial is registered at ClinicalTrials.gov (NCT06841133). Any modifications to the protocol will be promptly submitted to the institutional review board for review and approval.

Before participation, all eligible individuals receive detailed information regarding the study objectives, procedures, potential risks, and benefits. Written informed consent is obtained from each participant after a full explanation of the study requirements has been provided. For participants with visual or literacy challenges, the consent form is read aloud verbatim by a trained RA, and their written signature is obtained. To ensure confidentiality, all collected data are deidentified using unique participant codes. Electronic data are stored on encrypted, password-protected servers, and physical documents are kept in locked cabinets accessible only to authorized investigators. Saliva samples are processed for cortisol analysis immediately after collection and destroyed thereafter to prevent unauthorized use or retention. All research personnel have completed training in ethical data handling and participant privacy protection according to international standards [76].

In this study, the experimental group will receive supplemental entertainment activities as interventions alongside routine activities, whereas the control group will receive only routine activities. After the trial, the control group will be offered the same interventions if interested without follow-up requirements.

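### A second, group-specific consent at allocation lets residents decline knowing their arm, and the analysis rule then leaves decliners out

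*Protocol article*

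**What the plan says.** Participant Enrollment describes two consents. The first is general: "Written informed consent is requested prior to enrollment". The second is tied to the arm: "For group allocation, participants obtain a group-specific information sheet and sign a corresponding consent form".

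Table 1 (the SPIRIT schedule) agrees. General consent is ticked at T-1, while "Group-specific informed consent" is ticked at T0, the same column as allocation.

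On baseline, Trial Design states: "Baseline evaluations of PWB, loneliness, happiness, relaxation, and salivary cortisol levels are conducted before randomization". Table 1, however, ticks only PWB and loneliness at T-1.

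Participant Allocation fixes the numbers at each centre: "30 eligible participants are randomly divided into 2 experimental groups and 1 control group in a 1:1:1 ratio, with 10 participants in each group". It also says: "The allocation sequence is produced dynamically by an independent statistician throughout the recruiting phase".

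The analysis set is defined in Statistical Methods: "Following the intention-to-treat principle, participants with intervention data will be included in the analysis". The same section makes the preliminary analysis a complete-case one. It offers mean imputation only for gaps within a scale.

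**The concern.** Every trial participant may withdraw. This plan adds something to that right: to stay in, a resident must give a fresh signature, before the first session and most naturally with the arm already known. The arms differ visibly. One is the centre's usual schedule, one is individual painting and calligraphy, and one is an 80-minute session that ends in a peer group. A decision to decline can therefore depend on the arm and on traits such as sociability or interest in art, which may also be related to happiness, relaxation and loneliness.

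The analysis rule turns such a refusal into an exclusion. Someone who declines at T0 attends no session and has no session-day measurements, so the rule removes that person even though it is labelled intention-to-treat. If refusals differ by arm, the analysed groups are no longer the randomised groups, and objectives 1 to 3 rest on comparing those groups. Blinded assessment does not help, because the loss comes before any post-allocation measurement.

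**Working it through.** **Order of events.**

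1. General consent: T-1 (Participant Enrollment, Table 1).
2. Baseline: before randomisation (Trial Design). By Table 1, PWB and loneliness are certain at T-1; the other three outcomes are first ticked at T1.
3. Allocation and group-specific consent: both at T0. Table 1 lists the consent row above the allocation row, and the text does not say which comes first. A sheet and form that match a group can be selected only once the group is known, so the natural reading is allocation, then disclosure, then second consent.
4. First session: T1.
5. Analysis: participants with data from the intervention, which for controls must mean the session-day measurements.

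A refusal at step 3 therefore falls after randomisation and fails the rule at step 5. The article does not say whether a decliner stays in the randomised set, is followed up, or is replaced.

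**Size.** The plan gives no refusal figure to reproduce, so the following only illustrates the range. The inputs from the article are 30 per arm (90 in 3 arms), a design effect of d = 0.92 and a 20% dropout allowance. The assumed inputs are a refusal fraction of 10% (3 of 30) or 20% (6 of 30) in one arm, and how far decliners differ from the rest. The 20% case equals the plan's allowance for all dropout, so it is a generous value for refusal alone.

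*Simple shift.* If a fraction f is lost and differs from the rest by δ, the mean of those remaining differs from the full-arm mean by f × δ. With δ = 1 SD:
- f = 0.10: 0.10 × 1 = 0.10 SD
- f = 0.20: 0.20 × 1 = 0.20 SD

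*Truncation model.* If decliners are the lowest fraction r on a trait that correlates ρ with the outcome, the bias is ρ × φ(z_r) / (1 − r), in SD:
- r = 0.10: φ(z) / 0.90 = 0.195; bias 0.058 at ρ = 0.3 and 0.097 at ρ = 0.5
- r = 0.20: φ(z) / 0.80 = 0.350; bias 0.105 at ρ = 0.3 and 0.175 at ρ = 0.5

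*Effect on a nominal 5% two-sided test* (other arm complete, SE = √(1/30 + 1/n), with n = 27 or 24):
- r = 0.10: SE = 0.265; error 5.6% (ρ = 0.3) to 6.6% (ρ = 0.5)
- r = 0.20: SE = 0.274; error 6.7% (ρ = 0.3) to 9.8% (ρ = 0.5)

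Across both models one arm shifts by about 0.06 to 0.20 SD. Against d = 0.92 this is 0.06/0.92 ≈ 7% to 0.20/0.92 ≈ 22%. With no refusals it is zero.

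**The case against.** Much of the opposing case stands.

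- **Consent and baseline already come before randomisation.** This is not a design that randomises first and asks afterwards. A reader might infer that residents were randomised without knowing the options, but the documents do not support that. Ethical Considerations says "Written informed consent is obtained from each participant after a full explanation of the study requirements has been provided", the forms are not shown, and the second sheet may give only arm-specific logistics.
- **Arm-driven withdrawal would exist anyway.** Participants cannot be blinded and may leave, so a single consent would not close this route. Only the additional refusal prompted by a second signature belongs to this step, and nobody knows its size.
- **Replacement is conjecture.** A reader might infer from the exact 10 per arm per centre, and the exact 90 recruited, that decliners were replaced. No passage says so, and over-recruitment is the plan's stated allowance for loss. What can be said is that the article does not make clear whether the 90 are those randomised or those who signed the second form.
- **The order within T0 is inferred.** The flow diagram, which might settle it, is not available.
- **There is no sign that refusal was common.** In the pilot 19 of 20 attended every session, and the one loss was for a family trip. Controls are offered the activities afterwards, which weakens the motive to refuse routine care. Neither fact measures refusal at allocation in this trial.

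What survives is the link between the two passages. Whatever the number of decliners, the stated analysis rule would remove them, and the article provides no way to see it.

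**Conclusion.** The concern holds as a matter of exposure, at moderate severity. A second consent at allocation, most naturally signed with the arm known, combined with an analysis set that depends on having data from the intervention, leaves the randomised comparison open to selection. The size is unknown: zero if nobody declined, and roughly 0.06 to 0.20 SD for one arm if 10% to 20% declined selectively. That range rests on assumed refusal rates, an assumed difference of 1 SD or assumed correlations of 0.3 to 0.5, and the inferred order of events within T0.

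Two stronger conclusions should be resisted. One is that bias has occurred; no refusal is documented. The other is a combined shift of 0.2 to 0.4 SD, which needs two arms each to lose 10% to 20% of opposite types with a full 1 SD difference. Nothing in the article points to that.

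**What to change.** Recruitment ended on August 20, 2025 and data collection on October 31, 2025. The consent step cannot be changed for these 90 participants, and deleting it from Table 1 would misdescribe what was done. Table 1 should keep it. The changes still available are:

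1. **Analysis set.** Replace the rule in Statistical Methods with all randomised participants, each in the allocated arm whether or not the second form was signed. State that this was specified after data collection ended.
2. **Reporting.** In the flow diagram, give by arm the number allocated, the number who declined the group-specific form and the number replaced, with replacements identified. State the order of allocation and second consent. If nobody declined, one sentence settles the point.
3. **Comparison.** Compare decliners with the rest on the T-1 baseline (PWB and loneliness by Table 1, plus the other outcomes if they were in fact measured then), as far as the general consent allows use of those data.
4. **Sensitivity analysis.** For decliners without outcomes, vary their assumed difference from the rest, for example from 0 to 1 SD in either direction by arm, and report whether the conclusions change. If refusals differ by arm, limit the conclusions accordingly.

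Any future use of the design should take one consent covering all three arms before baseline and randomisation.

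The cost is a few flow-diagram rows, one corrected definition and one sensitivity analysis. With analysis expected to conclude in April 2026 and the protocol version dated March 2, 2026, this was still practicable when the plan was issued.

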### Participant Allocation

The allocation sequence is produced dynamically by an independent statistician throughout the recruiting phase. Each research site serves as a randomization unit. Using the Minimization Random Program software (version 2.01) [54,55], 30 eligible participants are randomly divided into 2 experimental groups and 1 control group in a 1:1:1 ratio, with 10 participants in each group. The confounding variables are age and number of visits per month. A study found that happiness increases with age before the age of 75 years, but for those over 75 years, the probability of happiness begins to decrease. Therefore, participants will be categorized into age groups of 60 to 75 years and over 75 years [56]. The other confounding variable is the number of visits per month. Older people living in institutions tend to meet with family and friends more frequently, often having more positive and less negative feelings [57]. Hence, participants were classified as having visits 1 to 2 times per month or 3 or more times per month. The categories of confounding variables are shown in Table 2.

The researchers will recruit 30 participants from each institution, resulting in a total of 90 older adults (aged 60‐85 years; individuals with ≤1 year of residence) referred by health care providers. In each institution, the 30 participants are allocated into 3 groups—A, B, and C—comprising 10 participants each. Group A is administered Chinese art activities, group B is administered Chinese art activities and peer group participation, and group C receives routine care.

**Table 2. T2:** Categories of confounding variables in the minimized randomization program.

Confounding variable	Category 1	Category 2
Age (y)	60-75	>75
Monthly visit frequency	1-2 times	≥3 times

### Blinding

A double-blind design is impractical due to the characteristics of the art-based intervention; however, outcome assessors and data analysts will remain blinded to guarantee an objective review. RAs responsible for pre- and postintervention data collection remain uninformed of group assignments and will not engage in the delivery of the intervention. An unblinded RA manages randomization and intervention delivery but is excluded from data collection tasks. Data analysts receive solely anonymized participant codes devoid of any information regarding group allocation. All blinded staff are not able to obtain information on group assignments.

### Intervention

#### Chinese Art Activities

A systematic, structured protocol guide is followed for the implementation of the Chinese art activity intervention at all the research centers [58-60]. The program begins with a 10-minute instructional introduction presented through a preprepared Microsoft PowerPoint presentation exhibited on a wide screen. These sessions focus on the historical development, philosophical underpinnings, and essential brush-and-ink techniques of traditional Chinese landscape painting and calligraphy. Example artworks are displayed on the screen throughout the relevant instructional segments to demonstrate aesthetic principles and improve participants’ visual literacy. A 3-minute instructional movie is subsequently shown. An iPad (Apple Inc) is supplied and positioned on the desks of participants who indicate difficulties with reading the screen clearly. The movie systematically illustrates the creation of a landscape (meticulously chosen by teacher or professor) scene using novice-friendly brush techniques and color modification methods. Afterward, participants have 25 minutes to replicate or modify (brush and color) samples on rice paper using traditional tools such as wolf brushes, pine smoke ink, and mineral pigments. Personalized design through color changes or the addition of natural elements such as birds and flowers is intentionally promoted to enhance individual creative expression. The next calligraphy activity is arranging for these participants to write a short lyrical poem or motto with a consistent theme based on their own paintings. During this phase, participants are assigned individual desks and chairs and independently engage in Chinese painting and calligraphy creation. Therefore, it is difficult for participants to communicate with each other.

This intervention is implemented by one of our RAs. He is a university professor and has studied Chinese painting and calligraphy for 5 years. He also has experience in organizing group activities. Standardized training is required for him on Chinese art activity intervention procedures, protocols, and security precautions. A detailed summary of the interventional strategy for Chinese art activities is provided in Textbox 1.

Textbox 1.Details of the Chinese art activity program.
**Activity**
Traditional Chinese landscape painting and calligraphy
**Instruments used**
Pens, ink, paper, inkstones, and pigments
**Procedure and duration**
Preliminary understanding and familiarization (10 minutes)Creation of traditional Chinese landscape paintings (25 minutes)Chinese calligraphy creation (15 minutes)

#### Chinese Art Activities Combined With Peer Group Participation

The Chinese art activities with peer group participation intervention, supported by previous studies [51,61], consists of an 80-minute integrated session led by a single researcher (RA). On the basis of established recommendations that at least 4 participants are necessary for effective group interventions [62], the 10 participants in this arm are randomly divided into 2 groups of 5, each facilitated by 1 trained peer volunteer, resulting in 6 individuals per group including the peer volunteer.

Peer volunteers are recruited through self- and staff recommendation. The inclusion criteria are being aged over 60 years, having lived in the center for more than 6 months, having normal cognition, moving freely, having good communication skills, and being enthusiastic to participate. They are responsible for organizing and guiding participants to actively express themselves and encourage each other during the peer group participation phase. One week before the intervention begins, training on research objectives and intervention procedures is conducted through meetings. The training also includes researchers demonstrating communication skills such as organizing peer evaluations, encouraging expression, and strengthening practical abilities through simulated exercises and on-site guidance. The training simultaneously evaluates the competence of volunteers, screening qualified candidates to participate in subsequent interventions. This study will not provide financial compensation to peer volunteers. As an alternative, the research team will give them flowers.

The intervention begins with Chinese art activities that follow the established procedures. After the Chinese art activities are completed, peer group participation is immediately carried out. Peer volunteers organize members to showcase their works. They invite each member to elaborate on the significance of their work while promoting mutual appreciation among group members. Subsequently, participants are encouraged to exchange their works as gifts accompanied by handshakes, smiles, or nods. Finally, peer volunteers conclude the program by sharing personal stories highlighting adaptation to life at the older adult center. Textbox 2 contains information pertaining to the Chinese art activities and peer group participation interventional procedures.

The intervention is implemented 3 times within a week following the structure described in Textbox 2 for each implementation. However, the content of each art activity slightly changes, involving drawings of watermelons, peaches, and lychees to maintain participation.

This study is about entertainment activities, and there are no adverse side effects. The research will last for 1 week, so no midterm analysis will be conducted. The entertainment activity arranged by the center does not involve the termination of the research. Hence, there is no trial monitoring either.

Textbox 2.Details of the Chinese art activity and peer group participation program.
